### Primary outcome

4.1

*Anthropometric variables* were measured twice, and their average was considered for the analyses. Weight was measured using a scale (Seca 861) with the child in light clothing and barefoot. For height, a wall stadiometer (Seca 222) was used with children barefoot and upright while the sagittal midline touched the backboard. Children had to look straight ahead, and the line of sight had to be parallel to the floor.

*Body composition.* Body mass index (BMI) was calculated as weight (kg)/height (m)^2^. Waist circumference was considered as the mean of 3 measurements using a flexible tape at the midpoint between the last rib and the iliac crest at the end of a normal expiration. The percentage of body fat and fat-free mass were measured by using an 8-electrode Tanita Segmental-418 bioimpedance analysis system (Tanita Corp., Tokyo, Japan).^[24]^ Body fat and fat-free determinations were performed under controlled temperature and humidity conditions. In addition, the measurements were done before breakfast, after urination, and after a 15-minute resting period.

*Blood pressure.* Systolic and diastolic blood pressure and heart rate were measured in a quiet place and after a 5-minute resting period using an OMRON-M5-I device (Omron Healthcare UK Ltd.),^[25]^ and cuff size was used according to the child's arm circumference. We considered for analyses the mean of the 2 measures separated by 5 minutes each.

*Biochemical determinations.* Blood samples were drawn from the cubital vein between 9.00 and 10.00 am, and after a 12-hour fasting period. Two aliquots from each sample were frozen for future determinations that could be of interest for parents.

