### Co-primary outcomes

4.2

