### Sample size

5.1

The sample size was estimated by considering a 0.3 difference mean change between the IG and the CG in cardiorespiratory fitness, as has been reported in previous studies.^[42]^ The estimates were calculated considering an alpha error of 0.05 and statistical power of 0.80. In addition, a mean of 40 children was considered in each classroom with a 15% dropout rate. For sample size calculation, optimal design software was used and Donner and Klar's models were considered.^[43]^

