### Analyses of outcomes

5.2

After measurements, participants’ data will be entered into a database by 2 independent researchers. Blinding on handling data will be assured by separating measurements values from general participant's information. Statistical analyses will be performed in 3 waves. First, the effectiveness of the randomization processes will be checked by exploring outlier values, and the normal distribution of the variables using the Kolmogorov Smirnov test and graphical procedures (normal distribution plots). After checking the truthfulness of outliers and extreme values, these will be winsorized using the 1st percentile and 99th percentile of the distribution of variables. Before conducting the analyses, and after considering the missing at random or missing completely at random nature, children with missing data will be imputed using chained equations.

Second, mixed regression models^[44]^ will be used to assess the change between the baseline and final variable measurements. For these analyses, each variable will be considered as an independent variable, and the intervention as a fixed effect. In addition, the analyses will be adjusted for baseline data, age, sex, and school (cluster).

Finally, the previous analyses will be done using propensity score methods for comparing the IG and the CG in the scenario in which IG subjects have the same characteristics as the CG ones at the baseline. This statistical method allows each child in the IG to be matched with a child in the CG, by using a variable as reference.

Results will be considered statistically significant at *P* < 0.05. The analyses will be performed using version 9.2 of STATA14. Finally, statisticians conducting the analyses will be blinded to the participant's allocation.

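### Sections 4.1 and 4.2 give primary or co-primary status to some 30 or more variables, each tested at a flat P < 0.05, although the trial was sized on cardiorespiratory fitness alone

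*Protocol article*

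**What the plan says.** Section 4.1 is headed "Primary outcome", in the singular. Under it stand anthropometry, body composition, blood pressure and heart rate, blood markers, two derived indices and five fitness components. None is singled out.

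Section 4.2 is headed "Co-primary outcomes". It covers three executive functions and two school subjects, and then accelerometry, quality of life and motor competence.

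Section 5.1 bases the sample size on one outcome, a 0.3 "difference mean change between the IG and the CG in cardiorespiratory fitness". It adds: "The estimates were calculated considering an alpha error of 0.05 and statistical power of 0.80".

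Section 5.2 fits mixed models in which "each variable will be considered as an independent variable, and the intervention as a fixed effect". I take this to mean that each measured variable in turn is the modelled outcome. It then states that "the previous analyses will be done using propensity score methods for comparing the IG and the CG", and closes with the rule "Results will be considered statistically significant at" P < 0.05. The rule does not distinguish primary, co-primary and other variables.

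**The concern.** A primary label tells the reader which result decides the trial. Here it is spread over a whole measurement battery, so height, BDNF and the sit-and-reach test have the same standing as the outcome used for sizing. The article's emphasis also varies: the aims (section 2) put physical fitness first, in line with the sizing, whereas the abstract and discussion put fat mass first.

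If section 5.2 is followed as written, any variable in 4.1 or 4.2 that crosses 0.05 can be reported as a significant primary or co-primary finding. What is at stake is the false positive rate of such claims, and whether the trial has a defined result.

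**Working it through.** **Stated figure.** The article gives alpha 0.05 and power 0.80 for one comparison. It states no total sample size, intracluster correlation or unit for the 0.3, so the sample size cannot be reproduced. If 0.3 means 0.3 SD and the test is two-sided (both assumptions), 175 children per arm are needed before clustering, or 175 / 0.85 = 206 with 15% dropout. For a single test, 1 − 0.95^1 = 0.05, so the stated alpha is right for that comparison.

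**Count under 4.1**
- Anthropometry and body composition: weight, height, BMI, waist, body fat, fat-free mass = 6
- Systolic pressure, diastolic pressure, heart rate = 3
- Total cholesterol, triglycerides, HDL, LDL, glucose, apo A1, apo A2, insulin = 8
- HbA1c, C-reactive protein, BDNF = 3
- HOMA, metabolic syndrome index = 2
- Cardiorespiratory fitness, handgrip, long jump, speed-agility, flexibility = 5

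Total 6 + 3 + 8 + 3 + 2 + 5 = 27, or 25 if weight and height are treated only as inputs to BMI.

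**Count under 4.2**
- Executive functions 3 + school subjects 2 = 5
- Plus accelerometry 1, quality of life 2 (child and parent) and motor competence 2 domains = 10, or 13 if the five motor tests are counted singly

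**At least one false positive, independent tests:** 1 − 0.95^k.
- k = 25: 72%
- k = 27: 75%
- k = 32 (27 + 5): 81%
- k = 37 (27 + 10): 85%

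**Correlated tests.** The article gives no correlations, so a range is assumed. Test statistics were simulated as X_j = √ρ·C + √(1 − ρ)·e_j, where C is standard normal and shared by all tests and each e_j is an independent standard normal (200,000 draws). A two-sided hit is |X_j| > 1.96. A false benefit is X_j > 1.96, with every variable oriented so that positive means better.

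| ρ | 27 tests, two-sided | 27 tests, benefit only | 32 tests, two-sided | 32 tests, benefit only | 37 tests, two-sided | 37 tests, benefit only |
|---|---|---|---|---|---|---|
| 0.3 | 63% | 33% | 68% | 36% | 72% | 39% |
| 0.5 | 48% | 24% | 52% | 26% | 55% | 28% |
| 0.7 | 33% | 16% | 35% | 18% | 37% | 18% |
| 0.9 | 17% | 8% | 18% | 9% | 18% | 9% |

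The benchmarks for one test are 5% two-sided and 2.5% for benefit only. The expected number of false positives among 27 is 27 × 0.05 = 1.35, whatever the correlation.

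**Lower bound.** One test for each of the five aims in section 2 (fitness, fat mass, cardiovascular risk, executive function, academic achievement) would give 1 − 0.95^5 = 23% under independence.

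**Keeping all 27 primary and adjusting.** The Bonferroni threshold is 0.05 / 27 = 0.00185. With 175 per arm, 0.3 SD and no clustering, power per outcome falls from 80% to 38%. Adjustment across the whole set is therefore a poor substitute for choosing the primary outcome.

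**The case against.** **A multiplicity method may sit in an analysis plan that is not shown.** This is fair, and the absence of a method is not the point here. What stands is what the article itself fixes: the labels and one threshold for all variables. A separate plan with a single primary outcome would contradict this text.

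**The count is uncertain.** This stands in part. Accelerometry, quality of life and motor competence follow academic achievement under a subheading on executive functions, where they do not obviously belong; the layout may have lost subheadings. None of the three is in the aims, and accelerometry covers a subsample of 500. Table 2 is not visible and might classify the variables. Hence 25 to 27 primary, and five or more co-primary.

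**The variables overlap.** Weight, BMI and waist move together, as do glucose, insulin and HOMA. The independence figure is therefore an upper reference and the correlated range is the better guide. Inflation shrinks but remains.

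**Co-primary may mean that all must succeed.** That would remove the inflation, but the article does not say so, and it would be a strange rule for 30 or more variables in a trial sized on one.

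**Stronger readings.** A reader might infer that the article's stated 5% error is false. It is not: section 5.1 gives a per-comparison alpha for one outcome, and no family-wise 5% is claimed anywhere. A reader might also infer that nearly any outcome of the trial could be presented as positive. The figures do not support that: at correlations of 0.3 to 0.7, false benefit among 27 tests runs from 33% down to 16%. Nor should the propensity-score run be counted as a second independent set of tests, since it puts the same questions to the same data.

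**Conclusion.** The concern holds in a limited form. The article labels 25 to 27 variables primary and at least five more co-primary, tests each at P < 0.05, and sized the trial on one of them. The 0.05 is sound for cardiorespiratory fitness alone. Across 27 primary variables with no true effect, the chance of at least one significant result is 75% under independence and about 63% to 33% at assumed correlations of 0.3 to 0.7. For false benefit only, it is about 33% to 16%.

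These figures assume equal correlation between all test statistics, normality and no true effect on any variable. The actual correlations are unknown. At every correlation examined, up to 0.9, the rate exceeds that of a single test.

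**What to change.** Before unblinded analysis, name cardiorespiratory fitness from the 20-m shuttle run at June 2018 as the single primary outcome, because section 5.1 sized the trial on it. Apply the confirmatory P < 0.05 in section 5.2 to that outcome alone. Relabel the other variables in 4.1 and 4.2 as secondary and report them as estimates with confidence intervals.

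The article describes measurement in the past tense and analysis as still to come. The choice must therefore agree with whatever was prespecified earlier and should say so. If that record requires more than one primary outcome, list them exactly and control the family-wise error across them, for example with Holm's procedure.

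The cost is rewording of 4.1, 4.2 and 5.2, and fewer results that can be claimed as confirmatory. No data are lost.

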## Discussion

6

This paper states the rationale and methods of a cluster randomized trial aimed at testing the effectiveness of an after-school physical activity intervention (MOVI-daFIT!), designed as a HIIT program, on reducing fat mass and cardiovascular risk, and improving fitness and cognition, including executive function and academic achievement.

Since sedentary time and overweight prevalence among children have been increasing during the last decades, developing physical activity programs aimed at reducing both are a political interest and public health necessity.^[45]^ For this purpose, schools are suitable places to implement programs based on behavioral changes,^[5,16]^ but additional evidence is needed on how to benefit from the effects of physical activity on children's physical and mental health within these settings.

Previous physical activity programs have demonstrated some positive effects on cardiovascular risk factors, for example, blood pressure, cholesterol, waist circumference, and body fat^[46]^; however, these changes do not seem to be translated into lower BMI or overweight/obesity prevalence.^[47]^ Furthermore, physical activity programs have reported positive effects on children's cognition, metacognition, and academic performance.^[18,19]^ The benefits of physical activity programs on children's physical and mental health seem to be promoted by improvements on children's fitness,^[9]^ but it should be highlighted that a specific description of the physical activity characteristics (i.e., frequency, intensity, and duration) and their combination associated with greater health improvements is still needed. In addition, there is a lack of evidence on how the deliberated manipulation of task complexity impacts children's cognition.^[18]^

Echoing these calls, we have developed the MOVI-daFIT! program to translate into practice the WHO's physical activity children's recommendations.^[23]^ Each session was carefully detailed in advance and designed to achieve the moderate-to-vigorous daily recommendations of physical activity. Children were monitored to ensure the daily-intensity goal and the activities programmed per session were modified based on children's reports. Furthermore, activities included cognitive and coordinative demands needed to foster the positive effects of physical activity on children's cognition and to achieve the desired intensity. This approach helped us design more realistic physical activity sessions that could better fit into children's physical activity patterns and enhance the usefulness and transferability of our results.

Some strength points of this program are that it is developed within the school setting using school facilities, a familiar environment for children, but without requiring changes in the curriculum; the physical activity program takes parents’ opinions and preferences into consideration without overloading them; furthermore, it includes programmed and structured activities, which are easily reproducible; and activities are designed so each child reaches the daily goal without promoting competitiveness.

We should recognize some limitations. Although this is a randomized controlled trial, children, parents, and teachers could not be blinded regarding the allocation group and some bias could be derived from this fact. We tried to reduce this bias through the cluster-randomized design. In addition, the measurements and intervention program sessions were standardized by training the staff, but some variability could not be neglected. Finally, a program based on physical activity was designed without considering diet interventions, although diet behavior information was collected. We followed previous research considering that energy intake is not the main cause of overweight prevalence and that diet interventions could increase the obese/overweight prevalence.^[48,49]^
